### Suspension of research standards

3.4

Study suspension means that the clinical research has not been completed according to the plan, and all studies are stopped midway. The purpose of the study suspension is mainly to protect the rights of the subjects, to ensure the quality of the research, and to avoid unnecessary economic losses. Criteria for discontinuing the study are as follows:

1.If serious safety problems occur in the study, the study should be suspended at that time.2.Significant errors found in the clinical research protocol during the study make it difficult to evaluate drug effects, or there is an important deviation in the implementation of the research program and it is difficult to evaluate the drug effect after it continues.3.Beijing municipal Science and Technology Commission suspends the research for some reason.

### Sample size calculation

3.5

The sample size calculation formula is as follows: 

[figure not shown]

In the above formula, *N* is the number of samples in each group, *p*_0_ is the incidence of outcomes in the non-exposed group, *p*_1_ is the incidence of outcomes in the exposed group, *c* is the ratio of the number of non-exposed and exposed groups, *α* is an acceptable type I error, *β* is an acceptable type II error, and *Z*_α_ and Z_*β*_ can be determined by looking them up in the *Z* value table.

The 1-year survival rate is expected to be 22% in the non-exposed group and 45% in the exposed group. Assuming a non-exposed group and an exposed group sample ratio of 1:1, the required sample size is estimated by SAS 9.4 software ([name]) to be at least 134 cases in the 2 groups, based on a 2-sided alpha at a significance level of 0.05 and the test efficacy 1-beta of 80%. Meanwhile, considering a dropout rate of 15%, we concluded that a total of 148 patients would need to be recruited to ensure significant results.

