### Participants

3.2

All patients fulfilling the inclusion criteria will be recruited, and those who meet one or more of the exclusion criteria will be refused.

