### Determination of grouping

3.7

Patients will be divided into a non-exposed group (Western medicine treatment group) and an exposed group (integrated traditional Chinese and Western medicine treatment group), according to whether they will receive TCM treatment or not. The classification of the cohort is based on the time of exposure after all clinical data are collected, not set at the time of enrollment.

1.Western medicine treatment group: times of chemotherapy ≥2 courses.2.Integrated traditional Chinese and Western medicine treatment group: TCM treatment ≥12 weeks, times of chemotherapy ≥2 courses, TCM and Western medicine treatment can be performed simultaneously or before and after.

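### The stated 80% power rests on a 1:1 split that the enrolment and grouping rules do not secure; section 3.5 should give power over a range of splits

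*Protocol article*

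**What the plan says.** Section 3.5 (Sample size calculation) lists the group ratio as an input to its formula and sets it to equality: "Assuming a non-exposed group and an exposed group sample ratio of 1:1". The effect is given as "The 1-year survival rate is expected to be 22% in the non-exposed group and 45% in the exposed group". The total is "to be at least 134 cases in the 2 groups", at two-sided 0.05 and 80% power. After a 15% dropout allowance, section 3.5 concludes that "a total of 148 patients would need to be recruited to ensure significant results". No target per group, expected uptake of TCM or source for the ratio is given.

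Section 3.2 (Participants) describes open enrolment: "All patients fulfilling the inclusion criteria will be recruited".

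Section 3.7 (Determination of grouping) says that cohort membership is "based on the time of exposure after all clinical data are collected, not set at the time of enrollment". The exposed group needs at least 12 weeks of TCM and at least two chemotherapy courses. The non-exposed group needs at least two courses.

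**The concern.** The three sections do not fit together. The ratio enters the sample size as if it were a design parameter, but as written it is a result of the study, known only when follow-up is over. The total of 148 could be reached while the smaller group falls well short of the 67 that the calculation assumes.

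What is at stake is how a null result is read. A reader who takes 80% at face value may treat a non-significant comparison as stronger evidence against a benefit than the achieved split allows.

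**Working it through.** **Inputs.** From section 3.5: p0 = 0.22, p1 = 0.45, difference 0.23, two-sided alpha 0.05 (z = 1.960), power 80% (z = 0.842), 134 analysed, 148 recruited, 15% dropout. The splits are assumptions, because the document gives none.

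**1. The protocol's own figure.** With equal groups the mean proportion is p̄ = 0.335. Using the pooled variance in both terms:

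n per group = 2 × 0.335 × 0.665 × (1.960 + 0.842)² / 0.23² = 66.1, so 67 per group and **134 in total**, as printed.

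The usual form (pooled variance under the null, unpooled under the alternative) gives 65 per group, 130 in total. The printed figure is sound at 1:1.

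**2. Number left after dropout.** 148 × 0.85 = 125.8, about 126.

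**3. Power at other splits.** With n0 non-exposed, n1 exposed and p̄ their weighted mean:

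- SE0 = √[p̄(1 − p̄)(1/n0 + 1/n1)]
- SE1 = √[p0(1 − p0)/n0 + p1(1 − p1)/n1]
- Power = Φ[(0.23 − 1.960 × SE0) / SE1]

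Example, 134 analysed, three exposed to one non-exposed: n0 = 33.5, n1 = 100.5, p̄ = 0.3925, SE0 = 0.0974, SE1 = 0.0871. Then (0.23 − 0.1909) / 0.0871 = 0.449 and power = 67.3%.

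| Exposed share | 126 analysed | 134 analysed | 148 analysed |
|---|---|---|---|
| 25% (1:3) | 69.2% | 71.8% | 75.8% |
| 33% (1:2) | 75.3% | 77.7% | 81.6% |
| 40% | 77.8% | 80.2% | 84.0% |
| 50% (1:1) | 78.8% | 81.3% | 85.0% |
| 60% | 76.5% | 79.1% | 83.1% |
| 67% (2:1) | 72.8% | 75.6% | 79.8% |
| 75% (3:1) | 64.4% | 67.3% | 72.0% |

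Power is at least 80% for exposed shares of about 39% to 57% with 134 analysed, and about 31% to 66% if all 148 are analysed. The fully pooled variant that reproduces 134 agrees within 2 points at 1:1, 2:1 and 3:1 with 134 analysed.

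**4. Total needed for 80% power before dropout** (usual form): 130 at 1:1; 143 with one exposed to two non-exposed and 150 the other way round; 166 at one to three and 180 at three to one.

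**5. The planned log-rank test.** Section 4.3.4 compares survival by log-rank. Assume exponential survival in each group at the stated 1-year rates, and follow-up spread evenly from 16 months (entry at the end of June 2020) to 31 months (entry at the start of April 2019) up to 31 October 2021.

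- Hazard ratio = ln 0.45 / ln 0.22 = 0.527, so |ln HR| = 0.640.
- Expected proportion dying: 94% non-exposed, 78% exposed.
- Power = Φ[√(d·s(1 − s)) × 0.640 − 1.960], with d deaths and exposed share s.

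With 134 analysed: 93% at 1:1 (about 115 deaths), 89% to 91% at 2:1, and 83% to 86% at 3:1. Three exposed to one non-exposed has d = 110: √(110 × 0.1875) × 0.640 − 1.960 = 0.95, which gives 83%. At 4:1 it is 76% to 81%. With 126 analysed, 3:1 gives 81% to 84%.

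**The case against.** The strongest reply is that the two-proportion test is not the main comparison. The primary outcome is overall survival, compared by log-rank, and under exponential survival that test stays above 80% out to 3:1. This stands, and it rules out the tempting reading that an uneven split necessarily takes the study below its stated power. It does not remove the point: section 3.5 bases its power on 1-year proportions, the log-rank figures rest on an added assumption, and that test also loses 7 to 10 points between 1:1 and 3:1.

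Second, nothing shows that the split will be lopsided. A reader might infer heavy imbalance from the TCM and integrated hospitals among the 12 sites, but section 3.1 also lists cancer hospitals and a general hospital. The 12-week TCM requirement pulls the exposed share the other way. The document supports neither direction, and a 40:60 split costs only about 1 to 2 points.

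Third, 1:1 is openly labelled an assumption, and an article may leave sensitivity tables to the full protocol. Figure 1 and Tables 1 and 2 are also not shown, so a target per group cannot be excluded. This stands in part. However, a target per final group could hardly be enforced during enrolment when section 3.7 fixes the group only afterwards. The limitations section warns about the amount of data from the integrated group, yet section 3.5 makes no allowance for it.

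Finally, the one-sided test in section 4.3.4 would raise power at 134 analysed to 85% to 86% at 2:1 and 79% to 81% at 3:1. It contradicts the two-sided basis of section 3.5. That is a separate conflict to reconcile and does not support the stated calculation.

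**Conclusion.** The point holds in a limited form. The 134 cases and 80% power are computed correctly for 1:1, but the enrolment and grouping rules do not secure that ratio, and one power figure hides the dependence. On the protocol's own test the loss is negligible near balance, about 3 to 6 points at 2:1 and about 9 to 14 points at 3:1 with 134 analysed. The dropout allowance gives no cushion: the 126 left after the stated 15% give just under 80% even at 1:1. (Inflating 134 fully for 15% dropout would need 134 / 0.85 = 158; that shortfall is a separate matter.)

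These figures rest on the stated survival rates and on assumed splits. The document does not show that the study will be underpowered: the achieved split is unknown, and the log-rank test may well keep more than 80% if survival is near exponential.

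**What to change.** In section 3.5:

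- State the expected exposed share and its basis.
- Replace the single 80% with power at splits of 1:1, 2:1 and 3:1 in both directions. Give it at the evaluable number after dropout (126) as well as at 148; at 148 alone, 2:1 shows 80% to 82% and hides most of the shortfall.
- Give these figures for the 1-year comparison and for the planned log-rank test, with the survival and follow-up assumptions of the latter.

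In the results, report the achieved split and the precision it gives.

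The cost is a rewritten paragraph and a stated power that becomes a range with a less favourable lower end. No extra patients and no new case report form item are needed.

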### Diagnosis and treatment

3.6

Diagnostic and staging criteria

1.Staging criteria: Refer to the American Joint Committee on Cancer (AJCC) staging classification for pancreatic cancer (2010, 7th edition).2.Pancreatic cancer: There is a confirmed pathological diagnosis.3.TCM syndrome diagnosis and efficacy evaluation: Refer to the “Guidelines for Clinical Research of New Drugs of Traditional Chinese Medicine (2002)” published by China Medical Science and Technology Press and “TCM Oncology (2nd Edition)” published by China Traditional Chinese Medicine Press.

Treatment plan

Western medicine treatment: refer to the standard treatment in the NCCN Guidelines 2017: pancreatic adenocarcinoma

Chinese medicine treatment: TCM syndrome differentiation.

### Determination of grouping

3.7

Patients will be divided into a non-exposed group (Western medicine treatment group) and an exposed group (integrated traditional Chinese and Western medicine treatment group), according to whether they will receive TCM treatment or not. The classification of the cohort is based on the time of exposure after all clinical data are collected, not set at the time of enrollment.

1.Western medicine treatment group: times of chemotherapy ≥2 courses.2.Integrated traditional Chinese and Western medicine treatment group: TCM treatment ≥12 weeks, times of chemotherapy ≥2 courses, TCM and Western medicine treatment can be performed simultaneously or before and after.

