#### Overall survival (OS)

4.1.1

The primary outcome of this study is OS, which is from enrollment to patient death or the end of the study (October 31, 2021).

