#### Data analysis

4.3.4

All statistical analyses will be performed using Statistical Packages of Social Sciences software (SPSS). A one-sided test (validity) will be used for all major efficacy indicators, and *P* values ≤.05 will be considered statistically significant. The measurement data will be expressed as the mean ± standard deviation, and the count data will be expressed using frequency and percentage. For quantitative indicators such as age, it is necessary to check whether the data meet the precondition of normality and homogeneity of variance. If the above conditions are met, a *t* test of measurement data of group design will be adopted. If only normality and not homogeneity of variance are satisfied, the calibration *t* test of measurement data in group design will be adopted. Otherwise, the Wilcoxon rank sum test will be used. For qualitative indicators such as sex, the general chi-square test will be performed according to the statistical analysis method corresponding to the data of the contingency table. If there is a frequency with a theoretical frequency <5, Fisher exact test will be used to directly calculate the exact probability. For survival data, the survival limit will be used to calculate the survival times of 25%, 50%, and 75% of each cohort. The log-rank test will be used to compare the survival rate, and the corresponding survival curve will be obtained.

For the analysis of influencing factors of efficacy, the univariate Cox regression model will be adopted in the first screen (*P* < .10), and the screened variables will then be fitted to the multivariate Cox regression model (*P* < .05).

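### Group membership is earned by at least 12 weeks of TCM after the fact, while OS runs from enrollment, so immortal time alone can yield a significant TCM benefit

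*Protocol article*

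**What the plan says.** Section 3.7 (Determination of grouping) fixes both when and how patients are assigned: "The classification of the cohort is based on the time of exposure after all clinical data are collected, not set at the time of enrollment". The integrated group requires "TCM treatment ≥12 weeks, times of chemotherapy ≥2 courses", and "TCM and Western medicine treatment can be performed simultaneously or before and after". The comparator is defined as "Western medicine treatment group: times of chemotherapy ≥2 courses", with no 12-week condition. The section opens by saying that patients are divided by whether or not they will receive TCM.

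Section 4.1.1 sets the clock: "The primary outcome of this study is OS, which is from enrollment to patient death or the end of the study". Section 4.3.4 (Data analysis) adds that "The log-rank test will be used to compare the survival rate" and that "A one-sided test (validity) will be used for all major efficacy indicators", with significance at P ≤ .05. It also describes Cox models with univariate screening for factors that influence efficacy.

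The article mentions no landmark, delayed entry or time-dependent exposure. Section 5.2 (Limitations) names small sample size, short duration and funding, but not this.

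**The concern.** Membership of the integrated group depends on what happens after time zero. To be classified there, a patient must live long enough to accumulate 12 weeks of TCM and two chemotherapy courses. If TCM follows chemotherapy, the wait is longer still. The Western group has a much shorter qualifying period. Because OS starts at enrollment for both, the difference in qualifying time is survival that TCM is credited with but did not produce.

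Patients who start TCM and die or stop before week 12 are not clearly placed. By the numbered criterion they satisfy the Western definition, which moves early deaths into the comparator. By the opening sentence they have received TCM and fit neither group, so they would be dropped, which removes early deaths from the TCM side. Both handlings favour TCM.

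The primary comparison is therefore tilted towards TCM by construction. A positive log-rank result could not be told apart from the grouping rule.

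**Working it through.** **Inputs from the article.** One-year survival 22% (non-exposed) and 45% (exposed), two-sided 0.05, power 80%, ratio 1:1, at least 134 cases, 148 recruited (3.5). Median survival on Western medicine 6 to 11 months (Introduction). Accrual April 2019 to June 2020, taken as 15 months; end October 31, 2021, taken as month 31.

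**Assumptions not in the article.** Exponential survival, half of patients starting TCM, six weeks of survival needed for two courses (three and eight weeks also tried), and TCM counted from enrollment onward. Both handlings of patients with too little TCM are shown.

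**Step 1: the plan's own figure.** With pooled proportion 0.335, n per group = [1.96·√(2·0.335·0.665) + 0.8416·√(0.22·0.78 + 0.45·0.55)]² / 0.23² = (1.308 + 0.545)² / 0.0529 ≈ 65, so 130 in total. That is within 3% of the stated 134, so the design inputs are understood correctly.

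**Step 2: who cannot qualify.** 22% at 12 months gives a median of 12·ln 2 / (−ln 0.22) = 5.49 months. Twelve weeks is 2.76 months, and survival to then is 2^(−2.76/median):

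| Median (months) | Alive at week 12 | Dead before week 12 |
|---|---|---|
| 5.5 | 0.706 | 29% |
| 6 | 0.727 | 27% |
| 8 | 0.787 | 21% |
| 11 | 0.840 | 16% |

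None of these early deaths can appear in the integrated group.

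**Step 3: one-year survival with no TCM effect.** At the 22% baseline, S(6 weeks) = 0.840 and S(12 weeks) = 0.706.
- Integrated: 0.22 / 0.706 = 31.2%.
- Western, patients with too little TCM dropped: 0.22 / 0.840 = 26.2%.
- Western, those patients counted as Western: 0.22 / (2·0.840 − 0.706) = 0.22 / 0.974 = 22.6%.

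The grouping rule alone creates a gap of 5.0 or 8.6 percentage points.

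**Step 4: false-positive rate.** Null simulation with 148 classified patients, uniform accrual, the 3.7 rule, and log-rank on OS from enrollment (2,000 to 4,000 replicates per scenario). The two-sided column counts only rejections in favour of TCM.

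| Median | Weeks to qualify | Too little TCM | HR | One-sided .05 | Two-sided .05 |
|---|---|---|---|---|---|
| 5.5 | 12 | Western | 0.72 | 59% | 47% |
| 5.5 | 12 | dropped | 0.83 | 28% | 19% |
| 8 | 12 | Western | 0.78 | 41% | 29% |
| 8 | 12 | dropped | 0.87 | 19% | 11% |
| 11 | 12 | Western | 0.80 | 30% | 20% |
| 11 | 12 | dropped | 0.89 | 14% | 9% |
| 8 | 18 | Western | 0.63 | 82% | 71% |
| 8 | 18 | dropped | 0.76 | 43% | 31% |
| 11 | 18 | Western | 0.66 | 67% | 56% |
| 11 | 18 | dropped | 0.79 | 32% | 22% |

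At the 22% baseline with TCM after chemotherapy (18 to 20 weeks to qualify), the one-sided rate is 95% to 98% (counted as Western) or 63% to 74% (dropped). If two courses need only three weeks, the 12-week case at that baseline rises to 82% or 45%.

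In a further set (1,500 replicates, median 8 months), TCM starts uniformly over the first three months. Counting patients with too little TCM as Western gives HR 0.66, one-year survival 51% v 33%, and rates of 82% one-sided and 73% two-sided.

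**Step 5: control and correction.** With no survival requirement for either group, the simulation rejects in 4.8% of trials one-sided, so the inflation comes from the rule. With a 12-week landmark (alive at week 12, OS counted from there), the rate is 4.9% to 5.2% one-sided and 2.4% to 2.8% in the TCM-benefit tail of the two-sided test. The median HR is 1.00 at medians of 5.5, 6, 8 and 11 months.

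**The case against.** The strongest case on the other side concerns size.

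- **Handling.** Reading the opening sentence of 3.7 together with the numbered criteria, a patient with 1 to 11 weeks of TCM may fit neither group. Dropping such patients is then the natural reading, and it gives the smaller bias. This stands as a caution, and both handlings are shown. The opening sentence can be read as a general statement that the criteria make operational, but it does not settle where these patients go.
- **Assumptions.** With patients dropped, eight weeks for two courses, a mildly rising hazard (Weibull shape 1.4), 134 analysed and an 11-month median, the one-sided rate falls to about 8%. Across medians of 5.5 to 11 months that setting gives HR 0.93 to 0.95. The rate is still above 5%, so the direction survives.
- **The 18-point gap (51% v 33%).** It needs an 8-month median, delayed TCM start and reclassification. It should not be taken as the typical artefact against the planned 23 points. At the 22% baseline with TCM from enrollment, the gap is 5 to 9 points.
- **TCM before enrollment.** If it counted towards the 12 weeks, the bias would shrink for those patients. The article does not say that it does.
- **Eligibility.** Table 1 is not shown and may require a minimum expected survival. That would not guarantee actual survival to week 12.
- **Two-course rule and Cox model.** The two-course rule in the Western group offsets part of the bias and is already in the simulations. Adjusting for screened covariates does not reassign misallocated person-time.
- **Unseen analysis plan.** It could add a corrected analysis, and the same cohort could support one. But the grouping rule, the time origin and the test are stated in this article and together produce the bias.

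**Conclusion.** The concern holds and the plan is wrong as written. Retrospective grouping on at least 12 weeks of TCM, with OS from enrollment and a log-rank test, builds immortal time into the primary comparison. Under no effect, TCM qualifying at week 12 and six weeks for two courses, the one-sided false-positive rate is 14% to 59% and the HR 0.72 to 0.89 over medians of 5.5 to 11 months. Across all scenarios run, the rate goes from about 8% to over 99%.

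The size rests on the survival shape, when TCM starts, how long two courses take, and how patients with too little TCM are handled. The direction held in every scenario run, on the assumption that the 12 weeks accrue after enrollment. A significant result from the planned analysis could not be attributed to TCM.

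**What to change.** Amend 3.7 and 4.3.4 as follows.

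1. **Primary analysis:** a Cox model on enrolled patients with TCM as a time-dependent exposure. Person-time is unexposed until TCM starts (or until 12 weeks have accumulated, whichever is prespecified) and exposed afterwards.
2. **If the two-course condition is kept:** every patient enters the risk set on the date of the second course (delayed entry). This removes patients with fewer than two courses, so the analysed population is no longer everyone enrolled, and the text should say so.
3. **Sensitivity analysis:** a landmark at a fixed, prespecified time. Include patients alive then, classify by TCM status at that date, and count OS from the landmark.
4. **Patients with 1 to 11 weeks of TCM:** state that they contribute according to actual exposure time. State also whether TCM before enrollment counts.

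**Cost.** Rewording of two sections, TCM start and stop dates on the CRF (which may already hold them), and a standard model. The estimated effect will probably be smaller. The landmark version loses deaths before week 12, about 16% to 27% of patients at medians of 11 and 6 months, and so loses power. Neither method removes confounding by fitness to start or continue TCM, which still needs baseline adjustment.

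### Section 3.7 gives two conflicting exposure rules, so patients with some TCM but under 12 weeks could be analysed as non-exposed, as exposed, or not at all

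*Protocol article*

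**What the plan says.** Section 3.7 (Determination of grouping) of the protocol article contains three statements that have to work together.

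- The lead sentence forms a non-exposed and an exposed group "according to whether they will receive TCM treatment or not". This is a split between any TCM and none.
- The timing rule follows: "The classification of the cohort is based on the time of exposure after all clinical data are collected, not set at the time of enrollment".
- The numbered criteria come last. Item 1 reads "Western medicine treatment group: times of chemotherapy ≥2 courses" and says nothing about TCM. Item 2, for the integrated group, reads "TCM treatment ≥12 weeks, times of chemotherapy ≥2 courses, TCM and Western medicine treatment can be performed simultaneously or before and after".

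The primary outcome (section 4.1.1) is overall survival counted from enrollment, and section 4.3.4 compares the groups by log-rank test. Section 3.3 lets patients be withdrawn for poor compliance and asks for a last follow-up so that efficacy can still be analysed. It does not say in which group.

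**The concern.** The lead sentence cuts at zero TCM and the numbered list cuts at 12 weeks. The two rules agree for patients who never take TCM, but not for those who start and do not reach 12 weeks. No sentence in the text shown places those patients, and they are unlikely to be a random subset, since people stop because of intolerance, deterioration or choice.

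This contrast is the only exposure comparison in the study. Because grouping follows data collection, whoever applies the rule will already know who died. If poor-prognosis stoppers go to the control side, the control group looks worse and the TCM group better. If stoppers resemble other TCM patients, the same placement dilutes a real effect. Dropping them selects the TCM group on later persistence. The problem would remain even if the separate question of guaranteed survival time before 12 weeks were solved, because it also concerns patients who are alive when they stop.

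**Working it through.** **Step 1. The rules side by side**, for patients with at least 2 courses of chemotherapy:

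| TCM received | Lead sentence | Numbered list | Joint reading |
|---|---|---|---|
| None | Non-exposed | Item 1 only | Non-exposed |
| More than 0, under 12 weeks | Exposed | Item 1 only | Neither group |
| 12 weeks or more | Exposed | Items 1 and 2 | Exposed |

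Only the middle row has three different answers.

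**Step 2. The plan's own figure.** Section 3.5 states: "The 1-year survival rate is expected to be 22% in the non-exposed group and 45% in the exposed group". With two-sided alpha 0.05 and power 80%, the pooled two-proportion formula gives

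n = [1.960 × √(2 × 0.335 × 0.665) + 0.842 × √(0.22 × 0.78 + 0.45 × 0.55)]² / 0.23² = 64.9, so 65 per group and 130 in total.

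This is within 3% of the stated 134, so the planned effect of 45% − 22% = 23 points can serve as the benchmark.

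**Step 3. Assumptions for size.** These are illustrative, because the documents do not give the share of short TCM users. Section 3.5 plans 148 patients and says "Assuming a non-exposed group and an exposed group sample ratio of 1:1", so take 74 who start TCM and 74 who never do. Let 10% to 30% of starters stop alive before 12 weeks: 7 to 22 patients. Counted as controls, they make up 7/81 = 9% to 22/96 = 23% of the Western group.

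**Step 4. No TCM effect.** Both sets of 74 have 22% 1-year survival overall (74 × 0.22 = 16.28 survivors), and stoppers have 10%.

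| Stoppers | Integrated without them | Western with them | Spurious gap |
|---|---|---|---|
| 7 | (16.28 − 0.70)/67 = 23.3% | (16.28 + 0.70)/81 = 21.0% | 2.3 points |
| 22 | (16.28 − 2.20)/52 = 27.1% | (16.28 + 2.20)/96 = 19.3% | 7.8 points |

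If the stoppers are dropped, the Western group stays at 22% and the gap is 23.3 − 22.0 = 1.3 to 27.1 − 22.0 = 5.1 points. If they stay on the TCM side, both groups are at 22% and the gap is zero.

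**Step 5. Planned effect, neutral stopping.** TCM patients, stoppers included, have 45% and the rest 22%. Stoppers are counted as controls.

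- 7 stoppers: Western (16.28 + 3.15)/81 = 24.0%, difference 45 − 24.0 = 21.0 points.
- 22 stoppers: Western (16.28 + 9.90)/96 = 27.3%, difference 45 − 27.3 = 17.7 points.

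**Step 6. Power under a different assumption.** Fix 67 per group, which gives 81% power at 22% versus 45%. If short TCM users at 45% survival make up 10% to 30% of the non-exposed group, power falls to 72% to 49%. If they are at 33.5%, it falls to 77% to 66%.

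**The case against.** The strongest reply is that item 1 should not be read apart from the sentence before it. The lead sentence equates the Western group with the non-exposed group and defines that group by not receiving TCM. The list can then be taken as adding a minimum amount of treatment to each group, with patients below a minimum falling in neither, as already happens to those with fewer than 2 courses. This has force. For patients with 12 weeks or more of TCM it largely removes the apparent overlap between the two criteria.

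It does not settle the patients with less. Exclusion is a reasonable inference that the text never states, and step 4 shows that exclusion by later TCM duration can bias the comparison too.

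A reader might infer that section 3.7 actually assigns short TCM users to the controls. It does not: no sentence says so, and the lead sentence points the other way. The control placement is one of three readings.

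A reader might also argue that dropping 22 patients leaves 126, below the stated minimum of 134, and blame the grouping rule. But 22 of 148 is 15%, the dropout rate already allowed for in section 3.5. The shortfall arises because 148 does not cover 134 with 15% dropout (134/0.85 = 158), which is a separate matter.

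Table 1 and Figure 1 are not shown and may hold a further rule, and section 3.3 may remove some early stoppers. Neither would make the statements in section 3.7 agree.

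**Conclusion.** The concern holds as a conflict between two exposure rules, not as a fixed misassignment. Patients with at least 2 courses and more than 0 but under 12 weeks of TCM can be analysed as non-exposed, exposed or excluded, and the choice would fall after outcomes are known. Because the article does state its group definitions and they disagree, this is a contradiction and not detail left to another document.

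Under the assumptions of 74 starters and 10% to 30% stopping alive before 12 weeks, control placement yields a spurious gap of about 2 to 8 points when TCM has no effect and stoppers have 10% survival. It reduces the planned 23 points to about 21 to 18 when stoppers have 45% survival. The direction therefore depends on why patients stop. The stopping share and the stoppers' survival are assumptions without a source in the documents, so these figures show what the ambiguity could do and do not predict the result.

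**What to change.** Reconcile section 3.7 before any patient is grouped:

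1. Define the Western group as at least 2 courses of chemotherapy and no TCM during the study, so that the groups are mutually exclusive.
2. State before analysis that patients with more than 0 but under 12 weeks of TCM are never counted as non-exposed.
3. Keep those patients in the main comparison on the TCM side, with TCM as a time-dependent covariate in the Cox model and the time before TCM start counted as unexposed. Simply counting every starter as exposed from enrollment would credit late starters with survival time they had to accrue before starting.
4. Report TCM duration (none, under 12 weeks, 12 weeks or more) as a descriptive secondary breakdown only, since duration itself depends on surviving.

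The cost is rewording, one table and somewhat more analysis work. TCM duration is already needed for the 12-week rule and Cox regression is already planned in section 4.3.4, but TCM start dates must be available, and a log-rank test on fixed groups could no longer carry the main comparison alone. The estimated effect may also turn out less favourable.
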